### Intervention

Intervention practices will be provided with a modified version of the Macmillan eCDS tool on the BMJ Informatica platform, which will contain the G-O cancer eRAT (Fig. 1) embedded within the clinical system. This provides a drop-down box containing an interactive risk calculator, which can be opened at the GP’s discretion during the consultation. It allows additional symptoms to be entered and generates a value for the risk of a currently undiagnosed G-O cancer. The GP then decides on further management, which may be clinical review in primary care, referral to a GI specialist, or direct referral for gastroscopy. The G-O cancer eCDS will also display an on-screen prompt at the start of a consultation if the relevant symptom(s) with a total risk >2 % has (have) been entered within the previous 12 months. Macmillan has undertaken extensive development and has addressed many of the key issues identified in the systematic reviews of eCDS, particularly the problem of prompt fatigue [23].

**Fig. 1 Fig1:**
[figure not shown]
Positive predictive values (95 % confidence intervals) for gastro-oesophageal cancer in men and women over 55 years of age for individual risk markers and for pairs of risk markers in combination. The top figure in each cell is the positive predictive value when both features are present. The two smaller figures represent the 95 % CIs for the positive predictive value. These have not been calculated when any cell in the 2×2 table was below 5 (invariably this was because too few controls had both features). The yellow shading is for pairs of symptoms with a positive predictive value over 1 %, the amber shading is when the positive predictive value is above 2.0 %, and the red shading is for positive predictive values above 5.0 %. The cells along the diagonal relate to the positive predictive value when the same feature has been reported twice. Thus the back pain/back pain intersect is the positive predictive value for pancreatic cancer when a patient has attended at least twice with back pain

A clinician from the research team will also visit each intervention practice to deliver an implementation package developed from a review of relevant systematic reviews from the Cochrane Effective Practice and Organisation of Care Group, evidence on the barriers to implementation of decision-support tools in other disease areas, and normalisation process theory. This will include the same information as the presentation given to all practices by the LCRNs, along with specific details of how to use the eRAT. Within this, whilst emphasising the need to use clinical judgement in all cases, we will provide guidance on how to interpret the output from the eRAT based on the new NICE guidance for suspected cancer in primary care [27]. They may then wish to consider referral for patients who have a calculated risk of 3 % or more, whilst those with a calculated risk of less than 3 % may be better managed by review in primary care. This practice visit will then be supplemented by peer-to-peer support as required.

### Control practices

Patients presenting to the control practices with upper gastrointestinal (UGI) symptoms will experience the GP’s usual diagnostic approach. Usual care is being used as a comparator for this study to help determine the actual benefits above normal practice. GPs in both arms of the trial will be offered free access to the Cancer Research UK-funded Royal College of General Practitioners (RCGP) online learning module on cancer diagnosis and to an end-of-study feedback event accredited for Continuing Professional Development (CPD) purposes. Control practices that have or acquire the Macmillan eCDS tool will be required to disable the G-O cancer functionalities for the duration of the trial.

### Process and outcome measures

We will examine the following processes relating to the use of eCDS:Practitioner outcomes – the frequency and sustainability of the use of eRAT, the adherence to recommendations, and the attitudes to and role of eCDSService outcomes – referral rates; use of diagnostic pathways (2WW and direct access gastroscopy, conversion (proportion of referrals with cancer diagnosis)) and detection rates (proportion of G-O cancers referred through these routes); time from the first consultation to diagnosis with cancer (diagnostic interval); and the stage of cancer at diagnosis using the TNM systemHealth economic outcomes based on estimates of resource usePatient outcomes – the acceptability of the use of eCDS.

We will perform the following tasks to inform the selection of outcome measures and power calculations for a subsequent Phase III trial:Estimate the standard deviation for continuous outcomesEstimate the proportions for binary outcomes (e.g. the proportion of patients referred in the control arm)Estimate the recruitment and consent rates among those eligible for inclusionDetermine the feasibility of data extraction at follow-upExamine how closely the stage at diagnosis is related to treatment with curative intent to inform choice of primary outcome measure.

### Data collection procedures

#### Patient recruitment

Practice administrative staff will use a pre-specified search string to search their electronic medical records weekly in order to identify patients who have presented to a GP within the previous week with qualifying symptoms. The records of patients thus identified will be reviewed by a designated individual (GP or practice research nurse) to determine eligibility to take part in the study. Administrative staff will post or use Docmail to send an information pack (consisting of invitation letter, participant information sheet, consent form and a reply paid envelope) to eligible patients.

We will seek consent for access to primary and secondary care records for follow-up data and for qualitative interviews. Patients who wish to participate will return their completed consent forms to the research centre. The researcher will inform the practice if a consent form is received and whether consent was given for data to be used in the study. For those who consent to their data being used in the study, the practice will respond with the date of the index consultation and, in addition, for those in the intervention arm, will submit an age group (in 5-year increments of 55–59, 60–64, 65–69, 70–74, 75–79, 80–84, 85–89, and 90+), the gender, and whether or not the eRAT was used.

A database of patients identified by the search string and those invited to participate will be kept by each practice; this database will be updated on a weekly basis. Practice administrative staff will identify any patients who have not responded at 2 weeks after being sent the invitation. These patients will be sent a reminder letter using either post or Docmail. Further information on the process of patient recruitment is provided in Table 1.

**Table 1 Tab1:** Patient recruitment procedures

Step	Frequency	Person responsible
Patient consults with relevant symptom		
Search of computer records to generate list of patients with qualifying symptoms	Weekly	Practice admin staff
List reviewed for eligibility and exclusions	Weekly	Practice research nurse
Invitations sent	Weekly	Practice admin staff
Response from patient received by researcher		Researcher
Consent information to practice	Weekly	Researcher
Date of index consultation identified for each consenting patient sent to researcher	Weekly	Practice research nurse
Age group, gender, and use of eRAT (Y/N) identified for each consenting patient in the intervention practices sent to researcher	Weekly	Practice research nurse
Reminders sent	Weekly	Practice admin staff

Patient consent is not being sought for the use of the eCDS during the consultation. This is because the eCDS tool is used at the discretion of the GP to support his/her clinical decision making. This is consistent with previous randomised controlled trials of interventions in primary care [30, 31]. Use of the eCDS will not detrimentally affect patient care, as practitioners will still adhere to usual clinical guidelines.

#### Data collection

Academic research staff will visit GP practices every 6 months to extract data on participating patients to minimise any loss of data resulting from patient transfer or death. Staff will also visit gastroenterology units to extract data from secondary care patient records. All participants will be followed up for 6 months. Using data extraction templates, adapted from those developed by us for previous comparable studies, we will collect the information shown in Table 2.

**Table 2 Tab2:** The type of data collection from the two care sites

Primary care data collection
Demographic data
Date of first consultation
Duration of index (first) consultation
Dates of subsequent consultations before referral
Referral in the episode of care – Y/N
Type of referral (2WW; open access gastroscopy; routine out-patient department; emergency, other)
Date of referral
Co-morbidities
RAT used - Y/N
Date used
Duration of consultation when RAT used
Final diagnosis
Secondary care data collection
Type of referral (2WW; OAG; routine OPD; emergency, other)
Diagnosis
Date of diagnosis
Stage

Practice level data on direct-to-gastroscopy referral and conversion rates will also be collected. The East Midlands Knowledge and Intelligence Team will hold cancer waiting time data at the practice level on upper gastrointestinal (GI) 2WW referrals, conversion and detection rates, and emergency presentations.

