### Data analysis

#### Statistical analysis

Patient throughput will be summarised for the 16-month recruitment period. For *each trial arm,* we will record the (1) number of eligible patients, (2) number of eligible patients approached to take part in the study, (3) number of eligible patients that consented/are recruited to the trial, and (4) number of recruited patients for whom outcome data are collected.

We will report the percentage of all eligible patients who are recruited (participation percentage) and the percentage of recruited patients for whom outcome data are collected with 95 % confidence intervals. Separate reporting of the participation percentage by the trial arm will help identify any obvious recruitment bias resulting from randomising the practices before recruiting patients to the trial. However, we consider the risk of serious recruitment bias to be low because all eligible participants from intervention or control practices will be invited to participate, and this will be done by post after the index consultation, rather than during the consultation.

General practices in the intervention and usual-care arms will be described separately with respect to region (a factor used to balance the randomisation). Participating patients will be described separately within each trial arm with respect to relevant baseline demographic characteristics, using means and standard deviations (or medians and interquartile ranges) for continuous variables and percentages for categorical variables. No formal tests of significance will be used for these descriptive analyses.

It is not a primary objective of the study to obtain definitive estimates of the intervention effect on study outcomes. However, comparisons between the intervention and control arms using the intention--treat principle will be reported as ancillary analyses. A comparison of binary outcomes will be implemented using marginal logistic regression models using generalised estimating equations (GEEs) with information sandwich (‘robust’) estimates of standard error, specifying the correlation structure as exchangeable. In the case of rare binary events, the responses will be summarised using percentages only. Comparison of time-to-event outcomes will be carried out using marginal proportional hazards models with information sandwich (‘robust’) estimates of standard error.

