Binary outcomes will be reported using a percentage for each trial arm, an odds ratio for comparing the trial arms, a 95 % confidence interval, and *p*-value. Time-to-event outcomes will be presented as the hazard ratio, confidence interval, and *p*-value. Crude estimates of intervention effect and estimates adjusted for region and practice size will be presented. The following outcomes will be compared:For all patients○ Whether the patient is referred (binary)For all referred patients○ Whether the patient is referred via the 2-week wait pathway (2WW) (binary)○ Whether patient is referred via the direct-access pathway (binary)○ Whether the referred patients were diagnosed with cancer (conversion – binary outcome)For all patients with cancer○ Whether the diagnosed patients had been referred via the 2WW/direct-access pathway (binary outcome)For patients referred via the 2-week wait○ Cancer conversion rate (binary outcome)For patients referred via the direct-access pathway○ Cancer conversion rate – (binary outcome)For patients diagnosed with cancer○ Stage at diagnosis○ Treatment with curative intent (binary outcome),○ 1-year and 3-year survival○ Diagnostic interval (time from symptomatic presentation to cancer diagnosis)

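### Table 2 records no death, leaving or last-record date, so the listed data cannot yield the planned survival comparison or show who left follow-up early

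*Protocol article*

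**What the plan says.** In the protocol article, the Data collection section sends research staff to practices every 6 months to "extract data on participating patients to minimise any loss of data resulting from patient transfer or death". So transfer and death are recognised as the ways in which information will be lost. The section also states that "All participants will be followed up for 6 months" and, of the extraction templates, that "we will collect the information shown in Table 2".

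Table 2 is fairly detailed. Its primary care part covers demographics, comorbidities, consultation dates and durations, tool use and its date, final diagnosis, the date and type of referral, and a yes/no item, "Referral in the episode of care – Y/N". Its secondary care part covers type of referral, diagnosis, date of diagnosis and stage. Neither part has an item for death, leaving the practice, or the end of the observed record.

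The Statistical analysis section lists, among the outcomes to be compared in patients diagnosed with cancer, "1-year and 3-year survival". It also says: "Comparison of time-to-event outcomes will be carried out using marginal proportional hazards models". Referral is a yes/no outcome for all patients. The section will report, by arm, how many recruited patients have outcome data.

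**The concern.** A survival comparison needs to know who died and when, and for everyone else the date until which they were known to be alive. Even if survival is treated as a yes/no outcome at 1 and 3 years, it needs vital status at those times. The article lists its data items, names death as a threat to them, promises a survival outcome, and yet lists no item that records death. These statements do not fit together. A longer follow-up alone would not cure this, because a death in month 2 is not among the listed items either.

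The second issue is the end of observation. The article gives the proportion referred in the control arm as an example of a planning quantity for phase III (Process and outcome measures), and names the feasibility of data extraction at follow-up as something to be learned. With no leaving or last-record date, a negative referral entry can mean six months without referral or a record that stopped after a few weeks.

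The timing matters. Fields not extracted during the trial may not be recoverable, since the Data anonymisation section has personal data destroyed at the end of the study.

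**Working it through.** **1. Survival: outcome against listed items.**

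| Needed | Where it would come from | In Table 2? |
|---|---|---|
| Start (date of diagnosis) | secondary care part | yes |
| Event (death, with date) | either part | no |
| Censoring date (leaving or last complete record) | primary care part | no |

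The one outside source named in the Data collection section is practice-level data on urgent referrals, conversion and detection rates, and emergency presentations. It supplies no individual deaths. The follow-up window is also too short: 12 − 6 = 6 months short for 1-year survival and 36 − 6 = 30 months short for 3-year survival.

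**2. Diagnostic interval.** It is defined only for patients diagnosed with cancer. Its start (first consultation) and end (date of diagnosis) are both in Table 2. Every patient in that set has the event, so no censoring date is needed.

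**3. The plan's own figures.** These reproduce and are not touched by this point. Sample size gives 30 practices per arm, 1800 patients aged 55+ per practice, 16 months, 80% identifiable and 80% consenting:
- 30 × 1800 × 16/12 × 0.80 × 0.80 = 46,080.
- Participants: 46,080 × 0.028 = 1290 to 46,080 × 0.040 = 1843 (stated 1292–1843).
- Gastroscopies: 46,080 × 0.017 = 783 (stated 780).
- Cancers: 783 × 0.04 = 31.3 per arm (stated 32).

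**4. Size of the referral effect.** The article gives neither a leaving rate nor a referral proportion, so everything here beyond the 3000 participants in the Abstract is assumed. The calculation also supposes that each leaver not yet referred is entered as not referred, and that every leaver would otherwise have stayed at risk of referral.
- Assume 2% to 6% leave within 6 months: 3000 × 0.02 = 60 to 3000 × 0.06 = 180 leavers.
- Assume 50% are referred in all, half of them at the index visit and the rest evenly over 6 months, with leaving times uniform over the window.
- Observed referral among leavers: 0.25 + 0.25 × 0.5 = 0.375, a shortfall of 0.125.
- Patients wrongly entered: 60 × 0.125 = 7.5 to 180 × 0.125 = 22.5, so about 8 to 23.
- Shift in the whole-sample proportion: 0.02 × 12.5 = 0.25 to 0.06 × 12.5 = 0.75 percentage points.

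**5. Sensitivity.** Take the gastroscopy share as a stand-in for the referral proportion p (780/1843 = 42% to 780/1292 = 60%), with a constant referral rate h = −ln(1 − p) over the window and uniform leaving. Observed referral among leavers is then 1 − p/h: 23% for p = 42% and 35% for p = 60%. Multiplying the shortfall (19 to 26 points) by the leaving rate gives:

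| Leavers | Downward shift, percentage points |
|---|---|
| 1% | 0.2–0.3 |
| 2% | 0.4–0.5 |
| 5% | 1.0–1.3 |
| 10% | 1.9–2.6 |

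For scale, with 1500 patients per arm (3000/2) and a proportion of 50%, the 95% half-width is 1.96 × √(0.25/1500) = 2.5 points before any allowance for clustering.

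**The case against.** The strongest reply is that this is an article, not the full protocol. Table 2 is captioned as showing the type of data, some entries are broad, and the templates are not shown, so a death or leaving date may well be on them. That lowers certainty, but it does not remove the conflict: the body text presents Table 2 as what will be collected, and nothing shown supplies the missing items.

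A second reply is that the survival problem is mainly one of follow-up length, and that Trial objectives assigns the examination of survival to phase III. The first half stands in part: a death date collected only within 6 months does not give 1-year or 3-year survival, so the horizon must be reconciled too. The second half does not help, because survival is still listed as a comparison in this trial.

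Third, arm comparisons are ancillary and the trial is not powered for hypotheses. This limits the consequence, but does not make the outcome obtainable.

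A reader might also go further and infer any of the following, which the document does not support:
- *That early leavers are scored as not referred.* No passage says so. Loss of data may mean a missing record, and the analysis counts recruited patients with outcome data. What holds is that the listed items cannot separate the two situations.
- *That every leaver is mis-scored.* On the assumptions above, 37.5% of leavers are already correctly recorded as referred. A patient who dies unreferred was truly not referred. Only those who would have been referred after transferring are wrong.
- *That no time-to-event model has a valid censoring date.* The diagnostic interval needs none.
- *That leaving differs between arms.* Nothing in the article indicates it.

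**Conclusion.** The point holds for survival and, more mildly, for the end of observation. As the article is written, the survival comparison cannot be produced from the listed data: death and censoring dates are absent, and the 6-month window ends 6 and 30 months before the two horizons. This rests on the text alone and needs no numerical assumption, but it is subject to what the unseen templates contain.

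For referral, the gap is one of interpretation more than of bias. On the main assumptions (2% to 6% leaving, 50% referred, half of these at the index visit) the shift is about 0.25 to 0.75 points, or 8 to 23 patients of 3000. The second set of assumptions gives somewhat more, 1.0 to 1.3 points at 5% leaving. Both overstate the effect to the extent that leavers are deaths or are recorded as missing. Up to 5% leaving, the shift stays below the sampling uncertainty of one arm's proportion. No sample-size figure changes.

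**What to change.** - Add three items to the primary care part of Table 2: date of death, date and reason of leaving the practice, and last date on which the record was complete. Extract them at the visits already planned. If the templates already hold them, listing them in Table 2 is enough.
- Measure survival from these dates, censoring at the leaving or last-record date.
- Report the number of early leavers by arm, with reason, beside the referral proportion.
- Reconcile the 6-month follow-up with the 1-year and 3-year outcomes: either obtain death dates to those horizons, or limit the survival outcome to what the follow-up supports.

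The cost is a few extra fields and slightly more analysis work. Only obtaining death dates to 1 and 3 years costs more, since it needs record access beyond 6 months and a check that consent and the data-destruction timetable allow it.

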## Trial objectives

The objectives of this trial are provided below:To optimise an intervention based on the use of the G-O cancer eCDS tool, establish its acceptability, and collect relevant data to inform the design of a subsequent definitive phase III trial.To obtain preliminary evidence on the effectiveness, implementation, and cost-effectiveness of the G-O cancer eCDS tool.

At the end of this phase II trial, we will have optimised the intervention and established its acceptability [25]. We will have also generated new knowledge on the process outcomes of the eCDS in primary care and its impact on resource utilisation and healthcare costs. In a subsequent phase III trial, we will examine the effect of the eCDS on G-O cancer stage at diagnosis, on surgical treatment, and on survival.

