### Practice recruitment

GP practice recruitment will be supported via the Local Clinical Research Networks (LCRNs), who will approach practices in the designated geographical regions, favouring Research Site Initiative (RSI) practices. Recruitment will focus on RSI practices because these practices have an ongoing commitment to research and, generally, have allocated research nurse time. In practices that do not have funded research nurse time, a research nurse from the LCRNs, if possible, may be funded to support the study. Representatives from the LCRNs or study team will visit all practices interested in participating and deliver a short presentation covering the background, aims, and design of the trial. Patient recruitment will take place over 16 months or until the required number of participants has been obtained; whichever is shorter.

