### Data anonymisation

All participants will be assigned an anonymous participant code, which will be used to pseudo-anonymise all data-collection forms. The key will be stored separately and will only be accessed by the local research team. Interviewees will be given a pseudonym, so they remain anonymous in the reporting of the qualitative data.

All personal data will be securely destroyed at the end of the study.

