## Discussion

The objectives of this trial are to optimise the intervention and establish the acceptability of both the intervention and randomisation, confirm the suitability and selection of outcome measures, finalise the design for the phase III definitive trial, and obtain preliminary estimates of the intervention effect. These outputs need to be obtained before conducting a definitive trial, which would determine the effect on patient outcomes (the stage at diagnosis, treatment with curative intent, 1-year and 3-year survival, and diagnostic interval), resulting from the introduction of the eCDS into general practice for suspected G-O cancer.

We will use the Medical Research Council framework for the design and evaluation of complex interventions [25, 33, 34]. We are conducting a phase II, exploratory, cluster-randomised controlled trial to evaluate an eCDS tool for suspected G-O cancer (the e-RAT [3]).

The use of the eCDS in intervention practices may result in a change in practice activity levels for gastroscopy. The direction of effect is uncertain, since any increase in activity may be offset by fewer unnecessary referrals. An absolute 10 % increase in gastroscopies in the intervention arm would constitute an additional 32 gastroscopies in each network area.

Public awareness campaigns for G-O cancer have been run as part of the Be Clear on Cancer campaign and resulted in an increase in GP consultations and referrals. If such a campaign runs in either or both of the two recruitment areas during the recruitment period, we will monitor and describe it.

New NICE guidance on the investigation of possible cancer was published in July 2015 after the study was designed and ethical approval was obtained but before recruitment had begun. The NICE guidance was based in part upon the research underpinning the eRAT, so control practices (if they fully adhere to the new guidance) may offer investigative practice closer in nature to the intervention practices than was expected at the time of the trial design. Adoption of the NICE guidelines (NG12) may also occur at different rates between the different clinical commissioning groups.

This is one of the first trials of eCDS for the early diagnosis of symptomatic cancer and will be completed in 2018.

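### Follow-up is fixed at 6 months for everyone, yet 1-year and 3-year survival are on the list of between-arm comparisons, and 3-year survival also runs past the stated 2018 completion

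*Protocol article*

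**What the plan says.** Three parts of the protocol article bear on this.

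- **Follow-up.** Data collection states: "All participants will be followed up for 6 months". Research staff visit practices every 6 months to extract data. The one external source named there holds practice-level waiting-time data, not individual deaths.
- **Outcomes.** Statistical analysis introduces its list with "The following outcomes will be compared" and, for patients diagnosed with cancer, includes "1-year and 3-year survival". For time-to-event outcomes it says: "Comparison of time-to-event outcomes will be carried out using marginal proportional hazards models", reported as a hazard ratio with confidence interval and p-value.
- **Calendar.** Trial status dates the start of site recruitment to September 2015. Practice recruitment says: "Patient recruitment will take place over 16 months or until the required number of participants has been obtained; whichever is shorter". The Discussion says that the trial "will be completed in 2018".

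The same Statistical analysis section calls the arm comparisons ancillary, and Sample size says that the trial is not powered for hypothesis tests.

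**The concern.** The analysis list promises survival at 12 and 36 months, while the follow-up statement stops at 6. No section gives diagnosed patients a longer window or names an individual-level source of deaths. An article may leave out detail, but here it gives a definite duration for all participants, and two listed comparisons do not fit inside it.

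At stake is what the trial can report. If the list stands, the analyst must either omit two listed outcomes or assemble them from whatever later deaths happen to be in the notes. Such ascertainment would be incomplete and need not be equally incomplete in the two arms.

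**Working it through.** **1. Number of patients concerned (reproducing the plan's figure).** Inputs from Sample size: 30 practices per arm, 1800 patients aged 55+ per practice, 17 gastroscopies per 1000 per year, 16 months, 80% identifiable by READ code, 80% consent, 4% cancer yield.

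- Gastroscopies per arm: 30 × 1800 × 17/1000 × 16/12 × 0.80 × 0.80 = 783 (stated 780).
- Cancers per arm: 783.4 × 0.04 = 31.3 (stated 32). Both arms: 62.7 (stated 64).

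The plan's figure reproduces within rounding, so the survival outcomes concern about 64 patients.

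**2. Follow-up against the horizons.**

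| Outcome | Needed | Stated follow-up | Share of horizon covered |
|---|---|---|---|
| 1-year survival | 12 months | 6 months | 6/12 = 50% |
| 3-year survival | 36 months | 6 months | 6/36 = 17% |

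A patient who dies within 6 months has a known status (dead) at both horizons. A patient alive at 6 months has a known status at neither. If the 6 months run from the index consultation and survival is counted from a later diagnosis, the window is shorter still.

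**3. Calendar.** Month 0 is September 2015, the earliest possible first patient, because that date is for sites. Recruitment is taken at its full 16 months, and completion is read as December 2018 (month 39).

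| Event | Month | Date | By December 2018? |
|---|---|---|---|
| Last patient enters | 16 | January 2017 | yes |
| Last 6-month follow-up | 22 | July 2017 | yes |
| 1 year, last patient, from index consultation | 28 | January 2018 | yes |
| 1 year, last patient, from diagnosis at month 6 | 34 | July 2018 | yes |
| 3 years, first patient | 36 | September 2018 | yes |
| 3 years, last patient, from index consultation | 52 | January 2020 | no |
| 3 years, last patient, from diagnosis at month 6 | 58 | July 2020 | no |

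**4. Share of recruits who could reach 3 years.** With even accrual over 16 months, counted from the index consultation:

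- September 2015 to December 2018 taken as 39 months: (39 − 36)/16 = 3/16 = 19%.
- Start of September 2015 to end of December 2018 taken as 40 months: (40 − 36)/16 = 4/16 = 25%.

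A later first patient lowers these shares, and so does counting from diagnosis. A shorter recruitment period raises them: at 12 months they would be 3/12 = 25% to 4/12 = 33%. For every recruit to reach 3 years by December 2018, recruitment would have to be complete within 3 to 4 months.

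**5. Slack for 1-year survival.** 39 − 34 = 5 months. If the first patient enters more than 5 months after September 2015 and recruitment runs its full 16 months, the last 1-year status after a month-6 diagnosis also falls after December 2018.

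**The case against.** The strongest reply is that these are minor items. The arm comparisons are ancillary, the trial is unpowered, survival is one line in a long list, and neither trial objective depends on it. That stands, and it limits the severity.

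A second reply is that the full protocol or analysis plan may describe mortality linkage. It may, but the article says 6 months for all participants without exception. If longer follow-up exists, that sentence is wrong, so the passages need reconciling either way.

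A third is that a proportional hazards model can censor survivors at 6 months. It can, but the result is a hazard ratio for the first 6 months and not survival at 1 or 3 years. Six-monthly visits may mean that some records are read later than 6 months after entry, but that does not change the stated window.

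A reader might infer more than the document supports:

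- *That no patient's status would be observed.* Early deaths settle both horizons, so the loss is confined to 6-month survivors.
- *That linkage is ruled out.* The Data anonymisation section says "All personal data will be securely destroyed at the end of the study". That stops tracing afterwards but not vital-status checks before the study ends.
- *That survival has been reserved for phase III.* Trial objectives says "In a subsequent phase III trial, we will examine the effect of the eCDS on G-O cancer stage at diagnosis" and goes on to name survival, but stage is in the same list and is openly compared in this trial. Assignment to phase III does not exclude a preliminary comparison here.
- *That survival results would steer the choice of phase III outcome.* Process and outcome measures names the relation of stage to treatment with curative intent for that purpose, not survival.
- *That Table 2 proves deaths are not collected.* It lists no vital status or date of death, but it also omits treatment, which is a listed outcome. It may only be a summary.
- *That the unstated survival time origin, and any lead time, is an error.* The origin is commonly left to the analysis plan, which is not shown.

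**Conclusion.** The contradiction holds. Follow-up of 6 months for everyone cannot deliver between-arm comparisons of 1-year and 3-year survival. Status at both horizons is missing for every 6-month survivor among about 64 expected cancers.

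The two horizons fail to different degrees. One-year survival fails only on the follow-up window and could be recovered by about mid-2018 on the earliest calendar. Three-year survival also conflicts with the 2018 completion: the last recruits reach it in 2020, and only about 19–25% of recruits could reach it in time. That range assumes a first patient in September 2015, even accrual over the full 16 months, counting from the index consultation, and completion in December 2018.

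Severity is moderate. The inconsistency changes what the trial can report but not its primary objectives.

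**What to change.** Delete 3-year survival from the comparison list in Statistical analysis.

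For 1-year survival, choose one of two courses:

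- **Delete it as well**, so that the list matches the 6-month follow-up; or
- **Keep it** and amend Data collection so that vital status is extracted for diagnosed patients to at least 12 months after diagnosis, with date of death as a data item obtained before personal data are destroyed. On the earliest calendar this is feasible by about July 2018. If first recruitment was more than 5 months later and took the full 16 months, the completion date needs checking.

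Deletion costs only wording. Keeping 1-year survival costs one further record check on about 64 patients. Patient recruitment already seeks their consent to access to primary and secondary care records. The team should confirm that the consent covers the longer period.
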